## Abstract

**Background:**

In France, the rapid scale-up of buprenorphine, an opioid maintenance treatment (OMT), in primary care for drug users has led to an impressive reduction in HIV prevalence among injecting drug users (IDU) but has had no major effect on Hepatitis C incidence. To date, patients willing to start methadone can only do so in a methadone clinic (a medical centre for drug and alcohol dependence (CSAPA) or a hospital setting) and are referred to primary care physicians after dose stabilization. This study aims to assess the effectiveness of methadone in patients who initiated treatment in primary care compared with those who initiated it in a CSAPA, by measuring abstinence from street opioid use after one year of treatment.

**Methods/Design:**

The ANRS-Methaville study is a randomized multicenter non-inferiority control trial comparing methadone induction (lasting approximately 2 weeks) in primary care and in CSAPA. The model of care chosen for methadone induction in primary care was based on study-specific pre-training of all physicians, exclusion criteria and daily supervision of methadone during the initiation phase. Between January 2009 and January 2011, 10 sites each having one CSAPA and several primary care physicians, were identified to recruit patients to be randomized into two groups, one starting methadone in primary care (n = 147), the other in CSAPA (n = 48). The primary outcome of the study is the proportion of participants abstinent from street opioids after 1 year of treatment i.e. non-inferiority of primary care model in terms of the proportion of patients not using street opioids compared with the proportion observed in those starting methadone in a CSAPA.

**Discussion:**

The ANRS-Methaville study is the first in France to use an interventional trial to improve access to OMT for drug users. Once the non-inferiority results become available, the Ministry of Health and agency for the safety of health products may change the the New Drug Application (NDA) of methadone and make methadone induction by trained primary care physicians possible.

The trial is registered with the French Agency of Pharmaceutical Products (AFSSAPS) under the number 2008-A0277-48, the European Union Drug Regulating Authorities Clinical Trials.

Number Eudract 2008-001338-28, the ClinicalTrials.gov Identifier: NCT00657397 and the International Standard Randomised Controlled Trial Number Register ISRCTN31125511.

## Background

Since 1996, two opioid maintenance treatments (OMT) have been marketed in France for opioid dependence: methadone and buprenorphine. It is acknowledged that recommended doses of buprenorphine are less effective than methadone in retaining patients in treatment
[1]. Currently, methadone and buprenorphine are accessible through different models of delivery and consequently target different drug-user populations
[2]. Buprenorphine is prescribed mainly in primary care, whereas methadone can only be initiated in a methadone clinic (medical centre for drug and alcohol dependence (CSAPA) or in a hospital setting), where patients receive both comprehensive general care and care for psychiatric comorbidities. In addition, in France, a patient can start buprenorphine promptly (even after the first visit) in primary care, whereas methadone induction in a CSAPA can take between 2 and 4 weeks. This is due to the fact that in general the patient must often first complete a psychiatric evaluation and psychosocial and motivational assessments.

Despite the lack of official clinical guidelines about the specific drug(s) to be prescribed in first-line treatment, buprenorphine is prescribed more often and is more widely available in France through primary care. This is due to its safety profile. While the effectiveness of the two treatments at adequate doses (for buprenorphine, this means doses which are higher than those recommended) is comparable, the risk of overdose is lower in buprenorphine patients
[1]. As a consequence, buprenorphine is more accessible to individuals who are less severely opioid dependent
[3]. Although this model of care for opioid dependence has had a positive impact on HIV epidemics and overdoses in drug users in France, it is still inadequate in terms of reducing the spread of Hepatitis C epidemics (HCV)
[4]. Indeed, the persistence of risky behaviours among opioid-dependent drug users could be interpreted as a response to an inadequate model of care. Many do not have access to methadone because of a limited access to CSAPA. In addition, it has been shown that a proportion of buprenorphine patients, albeit marginal, administers the treatment by a non-indicated route, either intranasally
[5] or intravenously
[6]. Expanded access to methadone treatment for opioid dependent individuals through innovative models of care is a major challenge for the control of HIV and HCV infection. The study described here is based primarily on the identification of a possible model for methadone initiation in primary care. Although the long-term effectiveness of methadone induction in specialized centres on different outcomes, including opioid use, has already been proven
[7,8], it is expensive, access is inadequate and many patients perceive it as stigmatizing. For these reasons, we conducted a trial to assess the non-inferiority of the proportion of patients abstinent from street opioid in patients inducted in primary care versus those inducted in CSAPA after one year of methadone treatment.

## Methods/Design

### Pre-trial phase

The study was designed in response to a request by the French Ministry of Health which asked the AIDS agency (ANRS) to develop an experimental study which would evaluate the effectiveness of methadone in primary care.

The research unit responsible for conducting the study is the unit U912 of the National Institute of Health and Medical Research (INSERM) in Marseilles, under the scientific responsibility of [name].

Before designing the trial, a multidisciplinary working group which also included members of patients’ associations was set up by the ANRS.

One of the major points to decide upon was the identification of a model for primary care which could maximize access while minimizing the risk of overdose. This model was designed from previous experiences of methadone provision in primary care
[9] and particularly the Scottish experience
[10]. The main points retained were: 1) study-specific pre-training for primary care physicians; 2) a shared care model, based on the patient-primary care physicians-CSAPA-pharmacist network; 3) the exclusion of patients with triple codependence on opioids/benzodiazepines/alcohol, as screened by MINI; 4) the daily supervision at the local pharmacy during the initiation phase for patients starting methadone in primary care; 5) patient accountability for treatment intake and appropriate storage.

Several subgroups were charged with, respectively, preparing the guidelines for methadone prescription, updating the methadone drug-drug interactions manual and designing an information booklet for the patient.

### Participants

From January 2009 to January 2010, we recruited 195 men and women in 10 cities (Avignon, Bayonne, Besancon, Bordeaux, Boulogne, Le Havre, Marseille, Metz, Rouen, Strasbourg) who were all over 18 and less than 70 years old, opioid-dependent in accordance with the DSM-IV criteria, and with an indication for methadone treatment (patients seeking care for opioid dependence and methadone prescription naive for at least one month or patients receiving buprenorphine but needing to switch to methadone treatment for medical reasons). The only difference between this trial and some previous trials
[11,12] was that in our study patients who had triple dependence (opioids, benzodiazepines and alcohol) and those who could not be contacted by phone were excluded. The reason for excluding opioid-dependent individuals also presenting with benzodiazepine and alcohol dependence was based on the results of several studies which have shown an increased risk of overdose associated with benzodiazepine use and alcohol use
[13].

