### Outcomes and instruments

Multiple sources were used for data collection at screening (week preceding recruitment and first/seventh day after recruitment), at recruitment (day zero or month zero), induction (from the first to the second week of treatment) and maintenance (third, sixth and twelfth months). Data collection methods (ongoing) include face-to-face interviews, phone interviews using a Computer Assisted Telephone Interview
[18] and self-administered questionnaires, all adapted and validated for the type of information to be gathered.

The Opiate Treatment Index (OTI), a multi-dimensional questionnaire based on patients’ self-report
[19] is being used to measure Methaville’s primary outcome. This consists in measuring the proportion of all participants abstinent from street opioids after 1 year of treatment. Some secondary outcomes are also measured. First, retention in treatment and occurrence of overdoses are assessed. The prevalence of other HCV risk transmission practices is also documented using a series of questions extracted from a standardized questionnaire specifically adapted for this purpose - the Blood-Borne Virus Transmission Risk Assessment (BBV-TRAQ)
[20,21] - and also the questionnaire used by Lucidarme et al. in their longitudinal study
[22,23]. Other data about indicators relevant for the purpose of this study have been collected: depressive symptoms (using the CES-D questionnaire
[24]), suicidal risk (the Beck Hopelessness Scale
[25]), impulsivity (the Barratt Impulsiveness Scale), sensation seeking (the Brief Sensation Seeking Scale (BSSS)
[26]), tobacco dependence (the Fagerstrom test
[27]), alcohol consumption (the AUDIT questionnaire
[28]), pain assessment (the Brief Pain Inventory
[29]), adherence to methadone prescription, patient-health care provider relationship
[30], opioid withdrawal (the subjective opioid withdrawal symptoms scale (SOWS)
[31]), quality of life (the 12-item Short-Form Health Survey (SF-12)
[32]), Attention Deficit Hyperactivity Disorder (Adult ADHD Self-Report Scale 6 item version
[33]), urinary drug screening, and finally socio-demographic information on history of incarceration and contact with associations. Quality assurance and data security measures were established and approved for this protocol on the 21^st^ of May 2008.

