### Sample size

We used the proportion of all patients abstinent from street opioids after 1-year of methadone treatment for the sample size. Many studies have shown that 60% to 80% of opioid-dependent individuals treated with methadone completely stopped using street opioids after one year of treatment
[34-36]. The hypothesis for this study was that after one year of methadone treatment, the proportion of patients not using opioids in CSAPA would be 70%. Considering a margin of inferiority of 15% in the primary care arm, 200 patients needed to be recruited to investigate non-inferiority.

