### Statistical methods

The trial was initially designed as a non-inferiority trial aimed to show the non-inferiority of the proportion of *non-injectors* who started methadone in primary care compared to those who started it in a CSAPA. However, as the number of patients injecting opioids at recruitment was low, the primary outcome was changed as ‘the proportion of *patients abstinent from* of street opioids after 1 year’, and the dimension of the study was re-computed. These changes were approved by the Scientific Committee of the trial, the Independent Committee and the Ethical Committee (CPP).

Secondary outcomes are the occurrence of fatal and non-fatal overdoses and the percentage of retention in both arms. We also investigated the prevalence of other HCV transmission practices and the effectiveness of treatment in terms of adherence, social insertion, addictive behaviours, quality of life, psychiatric comorbidities, social insertion, reduction in criminal acts and cost effectiveness.

When data analysis is completed later in 2012, the computation of the 95% confidence interval for the proportion of patients abstinent from street opioids at M12 in the two arms will be based on Intention To Treat (ITT), with lost to follow-up considered as a therapeutic failure (opioid users). Additional analyses will be performed without ITT, focusing on the most recent available information about opioid use during treatment. Mixed generalized linear models analyses will be used to identify predictors of the different outcomes. Non-inclusion or non-termination biases will be controlled for using selection models - including Heckman type models
[37] - and other approaches to take into account for the drop out process
[38].

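### Participants may already be abstinent from street opioids at entry, which could make the 12-month comparison less sensitive to a deficit among those who were using

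*Protocol article*

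**What the plan says.** All references are to the protocol article.

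- **Participants.** Everyone must be "opioid-dependent in accordance with the DSM-IV criteria" and have an indication for methadone. Two routes meet the indication. The first is for "patients seeking care for opioid dependence and methadone prescription naive for at least one month". The second, a separate route for people already in treatment, is for "patients receiving buprenorphine but needing to switch to methadone treatment for medical reasons". The stated exclusions are triple dependence and not being reachable by phone. Neither route carries a condition of current street-opioid use.
- **Outcomes and instruments.** The primary outcome consists in "measuring the proportion of all participants abstinent from street opioids after 1 year of treatment". It is a status at one time point. It is not a change from entry and is not limited to those using at entry.
- **Sample size.** The 70% hypothesis for CSAPA follows a statement that "60% to 80% of opioid-dependent individuals treated with methadone completely stopped using street opioids after one year of treatment". The margin is given as "Considering a margin of inferiority of 15% in the primary care arm", without a derivation.
- **Statistical methods.** The comparison at month 12 is by ITT, with loss to follow-up counted as opioid use. The section also records that "as the number of patients injecting opioids at recruitment was low, the primary outcome was changed": the first endpoint concerned non-injection.
- **Randomization.** Allocation was not stratified.

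**The concern.** The population, the endpoint and the control rate do not fit together neatly. The control rate describes people who stopped, which implies that they were using when treatment began. The endpoint counts anyone who is abstinent at one year, and the stated entry criteria leave room for people who were abstinent from the start. A patient on buprenorphine who changes drug for a medical reason is the obvious example.

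The month-12 status of such a patient may say little about whether induction in primary care works as well as induction in CSAPA. If the arms differ less in this group than among entry users, the group pulls the overall difference towards zero while the margin stays at 15 points. In a non-inferiority trial that loss of sensitivity favours the claim. It matters here because the Abstract says that the result may lead to a change in the authorised use of methadone.

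**Working it through.** **The plan's own figure.** The Sample size section gives 200 patients but neither alpha nor power, so the figure can be neither confirmed nor called wrong. With 70% in both arms, a 15-point margin and 1:2 allocation, one-sided 0.025 with 80% power needs 330, and one-sided 0.05 with 70% power gives 198. The point here does not depend on this figure.

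**Inputs from the article.** CSAPA rate 70%; margin 15%, read as percentage points; 95% confidence interval; arm sizes 147 and 48 (Abstract).

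**Assumptions.** The interval is a two-sided Wald interval for the difference. Entry users are abstinent at month 12 in 70% (CSAPA) and 55% (primary care), a deficit exactly at the margin. A share *f* is abstinent at entry, of whom 90% are abstinent at month 12 in both arms. The article does not give *f*, so a range is shown.

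**Formulas.**
- CSAPA: p_C = 0.90*f* + 0.70(1 − *f*)
- Primary care: p_P = 0.90*f* + 0.55(1 − *f*)
- Overall deficit: Δ = p_C − p_P = 0.15(1 − *f*)
- SE = √[p_C(1 − p_C)/48 + p_P(1 − p_P)/147]
- Chance of declaring non-inferiority = Φ[(0.15 − Δ)/SE − 1.96]

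**Example, *f* = 20%.** p_C = 0.18 + 0.56 = 0.74; p_P = 0.18 + 0.44 = 0.62; Δ = 0.12. SE = √(0.74 × 0.26/48 + 0.62 × 0.38/147) = 0.0749. Then 0.03/0.0749 − 1.96 = −1.56, and Φ(−1.56) is about 5.9%.

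| Share abstinent at entry | p_C | p_P | Overall deficit (points) | SE | Chance of declaring non-inferiority |
|---|---|---|---|---|---|
| 0% | 0.700 | 0.550 | 15.0 | 0.0778 | 2.5% |
| 10% | 0.720 | 0.585 | 13.5 | 0.0765 | 3.9% |
| 20% | 0.740 | 0.620 | 12.0 | 0.0749 | 5.9% |
| 30% | 0.760 | 0.655 | 10.5 | 0.0731 | 8.9% |
| 40% | 0.780 | 0.690 | 9.0 | 0.0709 | 13.3% |

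**Sensitivity to the assumptions.**
- *Success among those abstinent at entry, 70% to 100% instead of 90%.* At *f* = 40% the chance runs from 11.8% to 14.5%.
- *Arm sizes.* The Research design section gives a 1:2 ratio, which 147 and 48 do not match; that is a separate matter. With 200 patients at 1:2 (67 and 133), the four non-zero rows become about 4.1%, 6.4%, 10.0% and 15.1%.
- *Arm difference among those abstinent at entry.* If they carry half the users' deficit (7.5 points), the chance is 3.9% at *f* = 20% and 6.2% at *f* = 40%. If they carry all 15 points, Δ = 15 at every *f* and nothing is diluted.
- *A larger deficit.* A 20-point deficit among users reaches the margin overall at *f* = 25%, since 20 × 0.75 = 15.

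**The case against.** The strongest case against has several parts, and much of it stands.

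- **Such patients can fail.** A reader might infer that anyone abstinent at entry is a certain success whatever induction does. The Statistical methods section rules this out: loss to follow-up counts as opioid use, and these patients can also relapse. The mechanism needs only a smaller arm difference among them, and that is an assumption.
- **Their number is unknown.** The article reports neither the share of switchers nor the share abstinent at entry. All must be opioid-dependent, the medical reasons for switching are undefined, and being on buprenorphine does not imply abstinence from street opioids. Their number may be small.
- **The stated hypothesis concerns all participants.** It is tempting to call the percentages above false non-inferiority rates of the trial. They are not. At a 20% share the true overall deficit is 12 points, inside the margin, so a declaration would be correct for the hypothesis as stated. It misleads only if read as applying to entry users. The all-participant population also suits the policy question, since switchers belong to those who would be inducted.
- **The margin and the earlier endpoint.** A reader might infer that the margin was derived from patients using at entry, or that the current endpoint repeats the fault of the first one. The article gives no derivation of the margin. It reports few injectors at recruitment and says nothing about few street-opioid users.
- **Balance.** Randomization balances the share abstinent at entry in expectation. This answers a charge of bias from imbalance but not one of lost sensitivity.
- **Documents not shown.** The full protocol may contain a current-use criterion, and the SAP may plan covariate adjustment or subgroup analyses. If so, one sentence in the article resolves the point. Their absence from a condensed article is not itself an error.

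What remains is the combination that the article does state: entry criteria without a current-use condition, a 12-month status in everyone, and a control rate taken from people who stopped.

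**Conclusion.** The point holds as a conditional loss of sensitivity. The stated criteria allow participants who already meet the primary endpoint at entry. If the arms differ less among them than among entry users, the overall difference is smaller than the difference among users, by the factor (1 − *f*) when those abstinent at entry show no arm difference at all. In that case, with a 15-point deficit among users, the chance of declaring non-inferiority rises from 2.5% to between about 3.9% and 13.3% for shares of 10% to 40%. The effect is weaker if they carry part of the deficit and absent if they carry all of it.

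The documents do not establish that dilution occurs or how large it is, and they do not show that the all-participant test has an inflated error rate. The point justifies an inexpensive addition to the analysis and no change to the primary hypothesis.

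**What to change.** Before the unmasking planned after the last month-12 interview:

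1. Keep the all-participant ITT comparison as primary.
2. Adjust its risk difference for street-opioid use at entry and for entry route (seeking treatment or switching from buprenorphine). This improves precision and deals with chance imbalance under unstratified allocation. It does not remove dilution, because the estimate still averages over those abstinent at entry.
3. Pre-specify the same 15-point comparison in participants using street opioids at entry, as a supportive analysis reported beside the primary result. It should not be a second pass/fail test, and the non-inferiority claim should not depend on an undefined judgement of consistency.
4. Report the number abstinent at entry by arm.

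The Blinding section says that the trial's statisticians are not masked, so the addition should be dated and documented.

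**Cost.** A few lines of analysis-plan wording and one further analysis, with no new patients. It assumes that street-opioid use at entry was recorded with the instruments already in use. The price is a wider interval among users. With 70% in both arms, the half-width for all 195 patients is 1.96 × √(0.21/48 + 0.21/147) = 14.9 points. With 20% abstinent at entry, about 38 and 118 users remain and the half-width is 16.7 points. This is a further reason to treat the user-only result as supportive.

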### Research design

This study is a multi-site, open-label, randomized controlled non-inferiority trial, comparing methadone induction in France in a CSAPA or with primary care physicians with an allocation ratio of 1 :2. The randomization procedure allocated patients to the two different types of prescriber for methadone induction, lasting approximately 14 days for both prescribers).

A pilot phase was first carried out at one site (Avignon CSAPA and local primary care physicians) at a “slowed” recruitment rate in order to identify and prevent possible future problems when the trial was extended to the other sites.

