### Intervention

#### Patient screening

The first visit took place when a patient willing to be treated for his/her opioid dependence came to a Methaville physician, either in primary care or in a CSAPA (see Figure
1). During this visit, the physician explained the study protocol to the patient and performed the trial screening to confirm the patient’s eligibility. If he/she was eligible to enter the study and provided written informed consent to participate, the physician then immediately called the centre of methodology and management (CMM) of unit U912 to randomize the patient into one of the two groups. Details were exchanged and at the end of the medical visit the participant knew where he/she had to initiate methadone: in primary care or in a CSAPA.

This study was approved by the Ethics Committee of Persons Protection in Paris, France.

The screening physician, whether in a CSAPA or in a primary care setting, provided the randomization setting to the patient: if the patient was randomized into the same type of setting at that where initial screening took place, he/she could initiate methadone where he/she was screened. Otherwise he/she had to go to the other type of setting.

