### Randomization

For allocation of the participants to a primary care or a CSAPA physician, a computer-generated list of random numbers was used within a secured centralized internet system. Randomization sequencing was not stratified by the CMM, which generated the randomization sequence by computer and provided the number by phone to the prescribing physicians when recruiting a patient into the study.

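### The stated 1:2 allocation does not agree with the reported 48 v 147 patients, which is almost exactly 1:3, and nothing in the article explains the difference

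*Protocol article*

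**What the plan says.** The Research design section describes an open-label non-inferiority trial of starting methadone in a CSAPA or "with primary care physicians with an allocation ratio of 1 :2". In the order given, that is one CSAPA patient for every two primary care patients.

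The Methods/Design paragraph of the Abstract gives the two groups as "one starting methadone in primary care (n = 147), the other in CSAPA (n = 48". The Participants section says "we recruited 195 men and women in 10 cities", and 147 + 48 = 195, so the totals agree with each other.

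On method, the Randomization section says that "a computer-generated list of random numbers was used within a secured centralized internet system" and that "Randomization sequencing was not stratified by the CMM". It mentions no blocking. Under Patient screening, the physician "immediately called the centre of methodology and management (CMM) of unit U912 to randomize the patient into one of the two groups" once eligibility and consent were settled, so allocation came before the first dose. Under Statistical methods, the primary analysis "will be based on Intention To Treat (ITT), with lost to follow-up considered as a therapeutic failure (opioid users".

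The article reports no change of ratio, no exclusions after randomisation and no patients who failed to start.

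**The concern.** The design ratio and the arm sizes cannot both be taken at face value without an unlikely chance imbalance. This is a conflict between two stated design facts, not a detail left to a fuller document.

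The cause matters. If the list was programmed at 1:3, or was changed to it, the article misstates a basic design parameter and the comparison itself is unharmed. If 48 and 147 count patients by where treatment began, or if some CSAPA allocations were dropped, the arms are no longer those created by randomisation. The design leaves room for this: allocation was known at the end of the screening visit, the trial was open-label, and a patient allocated to the other type of setting had to go elsewhere to begin. Because loss to follow-up counts as failure, non-starters dropped from CSAPA would be failures missing from the control arm.

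The smaller control arm also limits the precision of the non-inferiority comparison.

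**Working it through.** **Inputs.** Ratio 1:2, CSAPA to primary care (Research design). Arm sizes 48 and 147 (Abstract). Total 195 (Participants). CSAPA abstinence 70%, margin 15 points, planned total 200 (Sample size). A 95% confidence interval (Statistical methods). Assumed here: simple unblocked randomisation, a true rate of 70% in both arms, and one-sided alpha of 2.5% or 5%, since the article states no alpha or power for the sample size.

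**Observed ratio.** 147/48 = 3.06. CSAPA share 48/195 = 24.6%, exact 95% CI 18.7% to 31.3%, which excludes the 33.3% implied by 1:2.

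**Fit to 1:2.** Expected CSAPA = 195/3 = 65. SD = √(195 × 1/3 × 2/3) = 6.58. z = (48 − 65)/6.58 = −2.58. Exact binomial: P(48 or fewer) = 0.0052, two-sided p = 0.0097. The central 95% range for CSAPA is 52 to 78. Simple randomisation is the case most generous to chance; blocking would make the gap harder to explain.

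**Fit to 1:3.** Expected 195/4 = 48.75 CSAPA and 146.25 primary care. P(48 or fewer) = 0.49, two-sided p = 1.0.

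**Size of the gap if 1:2 was programmed.**
- Patients counted in the wrong arm, total fixed at 195: 65 − 48 = 17.
- CSAPA patients removed, 147 complete: 147/2 = 73.5 expected, and 73.5 − 48 = 25.5, so about 25 missing from a total of about 220.
- Both figures restore an exact 1:2 split. Chance could cover part of the gap: six more CSAPA patients (54 of 201) would bring the two-sided p to 0.052.

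**Precision.** Effective size = 1/(1/n₁ + 1/n₂): 36.2 at 48/147 and 43.3 at 65/130, which is 16% less information.

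**Power.** SE = √(0.21/n₁ + 0.21/n₂), where 0.21 = 0.70 × 0.30. Power = Φ(0.15/SE − z).

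| CSAPA / primary care | SE | 0.15/SE | Power, one-sided 2.5% | Power, one-sided 5% |
|---|---|---|---|---|
| 65 / 130 | 0.0696 | 2.155 | 58% | 69% |
| 48 / 147 | 0.0762 | 1.969 | 50% | 63% |

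At 48/147 the 95% half-width for the difference is 1.96 × 0.0762 = 14.9 points, about the whole margin.

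**Does the planned 200 reveal the ratio?** No. With the same unpooled formula, 1:2 gives 198 at one-sided 5% and 70% power, but 1:1 gives 202 at one-sided 5% and 75% power. At 80% power and one-sided 5%, 1:2 needs 261 and 1:3 needs 308. With alpha and power unstated, 200 can be neither reproduced nor tied to a ratio.

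**The case against.** The strongest reply is that the mismatch is a slip in one sentence. The arm sizes add to the number recruited, so the article shows no gap. The Abstract says the patients were to be randomised into these two groups, so 147 and 48 read naturally as the randomised arms, and 1:3 fits them almost exactly. A change of ratio is also conceivable: there was a pilot phase, and the study size was recomputed when the primary outcome changed, although neither account mentions the ratio. Most of this stands. It makes a misstated or altered ratio the simplest reading, but under that reading the Research design section is still wrong or incomplete.

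A reader might go further and infer that chance is ruled out, that about 17 CSAPA patients are missing, or that the intention-to-treat arms are already corrupted. The article supports none of these. A 1% event under simple randomisation is unlikely, not impossible. The figure of 17 belongs only to reassignment within a fixed total; removal implies about 25. No section reports removal, reassignment or non-starters. The Abstract's reference to starting methadone is compatible with a count of starters but does not show that it is one.

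Nor is the power difference a proven loss: if 1:3 was intended, 65/130 was never the plan.

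**Conclusion.** The contradiction is established: the stated ratio is 1:2 and the reported arms are 1:3.06. Under simple randomisation at 1:2 the two-sided probability of so large a departure is about 1%; at 1:3 the arms are almost exactly as expected. A wrong or changed ratio is the most economical explanation, but the article cannot settle the cause.

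Damage to the intention-to-treat comparison is a possibility to be excluded, not a finding. It would follow only if 48 and 147 count starters in place of randomised patients, or if allocations were removed.

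Relative to 65/130, the reported arms carry 16% less information, and power is lower by about 7 points, under a 70% rate in both arms, a 15-point margin and either alpha shown. The point needs correcting because the primary comparison depends on knowing what was programmed and who was randomised to each arm.

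**What to change.** Before the month-12 analysis, the coordinating centre should compare its randomisation list with the 195 patients and state the programmed ratio, with the date and reason for any change.

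- If the ratio was not 1:2, or did not stay 1:2, correct the Research design section and confirm which ratio the planned total of 200 assumed.
- If it was 1:2 throughout, account for the shortfall against both possibilities (about 17 reassigned, or about 25 missing), and analyse every randomised patient in the arm shown on the list. If the list itself produced 48 and 147, say that the imbalance arose by chance.
- In every case, report by arm the number randomised and, separately, the number who started methadone in each setting.

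The check needs no outcome data, so it can be done at once, even though the Blinding section says that statisticians and data managers already know the allocation. The cost is one reconciliation of an existing list and a corrected sentence, plus a patient-by-patient account if the list and the arms disagree.
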